#### Screening

After the research team receive consent to contact and the associated contact details, they will arrange a telephone/videoconferencing screening appointment with the parent/guardian or adolescent (if they are 16 years and over). This screening approach has shown to be effective in previous trials of similar interventions [42, 43]. At this point, the following details will be recorded: contact details, age of depression onset and brief clinical history, previous contact with healthcare services, previous/current medications or therapy for depression, access to Internet/PC/Mac/laptop/smartphone, other diagnoses, and inclusion/exclusion criteria. The researcher will outline the time commitment involved in the trial at this stage. Adolescents meeting any exclusion criteria or not meeting all inclusion criteria at this time point will not be invited to the baseline assessment. If the adolescent is not eligible for the study or does not wish to attend a baseline appointment, the researcher will record the reason for nonparticipation. Reasons for not attending a baseline assessment will be recorded for CONSORT reporting.

#### Baseline and consent appointment

Families who meet the initial eligibility screening criteria and who are willing to attend a Microsoft Teams baseline appointment will be asked to complete a DAWBA [41] assessment online prior to the baseline appointment. Only the parent/guardian will complete the DAWBA.

Adolescents and one of their parents/guardians will be invited to attend a remote baseline appointment via Microsoft Teams. At this appointment, the details collected over the telephone/videoconference for the patient will be checked. The researcher will complete the consent process with the adolescent and their parent/guardian, and they will be consented into the trial. During this assessment, the researcher will send a live link to participants on Microsoft Teams where the participant will have an opportunity to read the information sheet again and then complete the consent form. The researcher will complete a paper or online version of an intellectual disability screening measure (Child and Adolescent Intellectual Disability Screening Questionnaire [CAIDS-Q]) [44] and the PHQ-A with adolescents to confirm eligibility. The researcher will then complete paper or online versions of all baseline measures with eligible participants. The participant will be given their study ID at the point of randomisation, at which point they are enrolled into the study. A log will be kept matching screening identification (IDs) with study IDs. Randomisation will occur via REDCap at or just after the baseline appointment (i.e. within 2 weeks), prior to starting the trial. The method of randomisation is block randomisation, performed independently of method of referral.

#### Additional eligibility assessments will be undertaken for those recruited from GP practices, NIHR Bio-Resource, and MyHealthE

As these sources will not have a suitably qualified NHS healthcare professional to confirm the presence of mild to moderate depressive symptoms, the chief investigator (CI), who is a consultant child and adolescent psychiatrist, will review screening and assessment data to confirm eligibility. If eligible, randomisation will be confirmed by the research assistant. This eligibility decision will be made within 2 weeks of the information being presented. A log will be kept recording the assessment outcome.

#### Ethical approval

The SPARX-UK trial obtained ethical approval from the South West-Cornwall & Plymouth Research Ethics Committee on 15 December 2022 (Ethics Ref.: 22/SW/0149) and has been registered with ISRCTN, trial number 15124804.

A schematic diagram of the trial design is shown in Fig. 1.

**Fig. 1 Fig1:**
[figure not shown]
Schematic diagram of trial design. Note: CAMHS, Child and Adolescent Mental Health Services; MHST, Mental Health Support Teams; GP, general practitioner; NIHR, National Institute for Health and Care Research; IS, information sheet; CTC, consent to contact; DAWBA, Development and Wellbeing Assessment; CAIDS-Q, Child and Adolescent Intellectual Disability Screening Questionnaire; CGI-S/I, Clinical Global Impressions Severity/Improvement; PHQ-A, Patient Health Questionnaire modified for adolescents; RCADS, Revised Child Anxiety and Depression Scale

### Study participants and sample size rationale

Participants in this trial are the adolescents, and it is also a requirement that one of their parents/guardians are also consented to the trial. One of the aims of this study is to estimate the variance of the primary outcome measure (change in PHQ-A), so that a sample size can be computed for a subsequent trial of intervention efficacy. There are multiple methods suggested for sample sizes in pilot studies, but here the numbers are reflecting the smallest sample size (pilot plus subsequent efficacy trial), for which 40 per arm is reasonable [45]. A sample size of 40 per arm should be sufficient to avoid under or overpowering the main study whilst not making the pilot study excessively large.

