### Objectives

The feasibility objectives of the trial are to examine the use and recruitment of SPARX in particular settings, specifically Child and Adolescent Mental Health Services (CAMHS), school-based Mental Health Support Teams (MHST), general practitioner (GP) practices, approved previous trial cohort databases (i.e. National Institute for Health and Care Research/NIHR BioResource), and resources (i.e. MyHealthE). The feasibility objectives of the intervention are whether supported SPARX has an added benefit on adherence (i.e. how many levels in total participants completed) and engagement (i.e. overall response to, sense of immersion and satisfaction with the intervention). Feasibility of the intervention will be determined by the proportion of participants completing at least four modules of SPARX, as this is deemed to be the minimum effective dosage given that is where the main therapeutic content is delivered. More than 80% completion would be considered feasible, whereas below 40% will be considered not to be feasible. For the likely outcome of completion rates falling between these limits, detailed analysis of trial data, including process evaluation qualitative interviews, will be used to inform the approaches that may improve adherence rates in subsequent trials. Value added by the supported SPARX intervention will be considered in terms of how much greater, if at all, the adherence rates are. The pilot objective is to estimate the variance of change in the primary outcome measure within groups (Patient Health Questionnaire modified for adolescents [PHQ-A] [38]) to calculate an appropriate sample size for the full definitive trial.

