## Methods

### Trial design

This trial is a single-blind, three-arm, pilot, and feasibility randomised controlled trial, with an embedded process evaluation. The research assistants who conduct the baseline and primary endpoint assessments are blinded. The study settings are CAMHS, MHSTs, GP practices, and two databases/resources (NIHR BioResource and MyHealthE). CAMHS are National Health Service (NHS) centres that assess and treat adolescents with emotional, behavioural, or mental health difficulties. MHSTs are a recent government initiative designed to support young people with mental health issues in education settings. GP practices are primary medical services in the UK that treat all common health conditions and refer patients to hospitals and other medical services for urgent or specialist treatment. The NIHR BioResource is a recallable resource of over 250,000 volunteers, with and without health conditions, who have agreed to take part in health-related research. MyHealthE is an online portal where parents and caregivers can complete routine outcome measures digitally, and as part of this system, parents can then give their permission to be contacted with invitations to take part in other research studies, that is, providing their consent to be contacted. All CAMHS, MHSTs, and GP practices will be based in England. We aim to recruit 120 participants (aged 11–19 years) in total. Participants will be followed up at weeks 4 and 8–10 after baseline. Participants will receive £20 worth of Amazon vouchers for each assessment time point completed.

Our protocol follows the Consolidated Standards of Reporting Trials (CONSORT) extension for randomised pilot and feasibility trials [39] and the Standard Protocol Items: Recommendations for Interventional Trials (SPIRIT) [40]. Please see Additional file 1 for our SPIRIT checklist.

This protocol has also embedded patient and public involvement (PPI) throughout its development, following recommendations from the NIHR and UK standards for public involvement (see: https://sites.google.com/nihr.ac.uk/pi-standards/home). More detail can be found below on how PPI has shaped this programme of work.

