#### Study population

Study participants will be adolescents aged 11 to 19 years with mild to moderate levels of depression.

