### Statistical methods

#### Quantitative analyses

Summary statistics will be presented for this trial using Microsoft Excel. No interim analyses are planned. Summary statistics, proportions, and standard deviations will be given to estimate the change in PHQ-A, variance, and recruitment rates (per month) in different settings and whether there is compliance (defined as the percentage completing four levels or more of SPARX). The primary pilot outcome is the variance in change in the primary outcome measure (PHQ-A). We will not stratify at this point because we are estimating variance, not effect, and we are assuming they are similar, although this will be checked. A full analysis plan will be made available before unblinding of data, and anything that is not planned will be considered data dependent and considered speculative [59].

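### The pilot outcome is the variance of raw PHQ-A change; if the definitive trial adjusts for baseline, that figure may overstate the number needed, so the residual SD should be reported too

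*Protocol article*

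**What the plan says.** The same quantity is named in four places in the protocol article. Objectives: "The pilot objective is to estimate the variance of change in the primary outcome measure within groups", with the stated use of calculating a sample size for the full trial. Study participants and sample size rationale: "One of the aims of this study is to estimate the variance of the primary outcome measure (change in PHQ-A"). The purpose given there is again the sizing of a later efficacy trial. Primary outcome measures, under the pilot outcome, gives the variance of PHQ-A change from baseline. Quantitative analyses: "The primary pilot outcome is the variance in change in the primary outcome measure (PHQ-A").

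Quantitative analyses also says that variances across groups are taken as alike: "we are estimating variance, not effect, and we are assuming they are similar, although this will be checked". It promises a full analysis plan before unblinding and says that anything outside the plan will be regarded as speculative. Table 2 has PHQ-A collected at baseline, 4 weeks and 8–10 weeks. The sample size rationale sets 40 per arm, with the aim of neither underpowering nor overpowering the main study.

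The Discussion says only that the later trial will compare outcomes with care as usual. It gives no analysis model, target difference, alpha or power.

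**The concern.** A trial with a baseline and a follow-up score can be analysed on the change score or on the follow-up score adjusted for baseline (ANCOVA). Each analysis has its own variance for the sample size calculation. The protocol carries forward only the first. If the definitive trial uses the second, the variance handed to it can be too large and never, in population, too small. The cost would be adolescents recruited beyond what the power target requires.

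The wording of the pilot outcome matters because providing this variance is the declared pilot objective, and because quantities added after the fact fall under the protocol's own rule on unplanned analysis.

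**Working it through.** **The plan's own figure.** Three arms of 40 give 3 × 40 = 120, which agrees with "We aim to recruit 120 participants". The 40 per arm rests on a cited method whose inputs are not given, so it cannot be re-derived. No sample size is stated for the definitive trial.

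**Inputs.** Let SD0 and SD1 be the within-arm SDs of PHQ-A at baseline and follow-up, and rho their correlation. The document gives none of them, so every value below is an assumption.

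**Step 1: the two variances.**
- Change: SD0² + SD1² − 2·rho·SD0·SD1
- Baseline-adjusted residual: SD1²(1 − rho²)
- Difference: SD0² − 2·rho·SD0·SD1 + rho²·SD1² = (SD0 − rho·SD1)², which is at least 0

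The difference is zero when SD0 = rho·SD1, that is, when the slope of follow-up on baseline is exactly 1.

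**Step 2: ratio of required numbers.** For a fixed target difference, alpha and power, the number needed is proportional to the variance, so the oversizing ratio is the ratio of the two variances. With SD0 = SD1 it reduces to 2(1 − rho)/(1 − rho²) = 2/(1 + rho).

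| SD0/SD1 | rho 0.3 | rho 0.5 | rho 0.7 |
|---|---|---|---|
| 1.0 | 1.54 | 1.33 | 1.18 |
| 0.8 | 1.27 | 1.12 | 1.02 |
| 0.5 | 1.04 | 1.00 | 1.08 |

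For example, SD0 = 4, SD1 = 5 and rho = 0.5 give 21.0/18.75 = 1.12.

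**Step 3: effect of restricted entry.** "Study participants will be adolescents aged 11 to 19 years with mild to moderate levels of depression", so the baseline spread is probably narrow. Under a linear model with constant residual variance, selecting on baseline leaves the slope b and the residual variance unchanged and shrinks only SD0. The excess is then (1 − b)²·SD0², which falls as SD0 falls.

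Suppose both unselected SDs are 5, so b equals the unselected rho. Suppose also that entry reduces SD0 to about 2.9, the SD of scores spread evenly over an assumed band of 5 to 14. Then SD0² = 8.41 and:
- rho 0.3: 0.49 × 8.41 / 22.75 = 18%
- rho 0.5: 0.25 × 8.41 / 18.75 = 11%
- rho 0.7: 0.09 × 8.41 / 12.75 = 6%

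If instead SD0 = 2.9, SD1 = 5 and rho = 0.5 hold within the selected sample, the excess is (2.9 − 2.5)²/18.75 = 0.16/18.75, about 1%.

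**Step 4: in numbers of participants.** Assume SD1 = 5, a between-arm difference of 2.5 points, two-sided alpha 0.05 and 90% power. Then n per arm = 2 × variance × (1.960 + 1.282)²/2.5², with rho = 0.5 and an adjusted variance of 18.75:
- SD0 = SD1: change variance 25, so 85 against 64 per arm
- SD0 = 0.8·SD1: change variance 21, so 71 against 64
- SD0 = 0.5·SD1: change variance 18.75, so 64 against 64

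In the first case, 85 per arm analysed with baseline adjustment would have about 96% power instead of 90%.

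**Step 5: sampling error.** With 120 participants pooled over three arms (117 df), the 95% interval for a variance runs from 0.79 to 1.32 times the estimate. With one arm of 40 (39 df) it runs from 0.67 to 1.65. In simulation with three arms of 40, the estimated adjusted variance exceeded the estimated change variance in 67% of runs at SD0/SD1 = 0.5 and rho = 0.5, where the population values are equal. It did so in none at SD0 = SD1 and rho = 0.5.

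**The case against.** The strongest reply is that nothing in the article commits the definitive trial to baseline adjustment. The sample size rationale treats change in PHQ-A as the outcome. If change is what the later trial analyses, its variance is the correct input. This stands, and it makes the point conditional. A reader might infer that the definitive trial will be oversized; the document does not support that.

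A second reply is that the correlation and the residual SD can be computed at any time, because PHQ-A is measured on the same adolescents at each visit, and that such detail belongs in the analysis plan. The first half is true, so it would be wrong to say that the pilot cannot supply them. But the article does not leave the quantity open. It names the change variance as the primary pilot outcome and treats unplanned analysis as speculative, which is a reason to name the residual SD in advance.

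A third reply is that any excess is conservative for power and may be no larger than the sampling error of the variance itself. This also stands. The cost is efficiency, not validity.

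One might also argue that recruiting only mild to moderate cases makes raw change perform especially badly, because a narrow range lowers rho. Step 3 shows the opposite: the narrower baseline SD reduces the excess.

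**Conclusion.** The point holds conditionally. The protocol fixes as its primary pilot outcome a variance that, in population, is never smaller than the baseline-adjusted one. If the definitive trial adjusts for baseline PHQ-A and is sized on the change variance, the number needed may be overstated by near 0% to about 54%. That range assumes rho between 0.3 and 0.7 and a baseline SD between half of and equal to the follow-up SD. In the selection example of Step 3 it is roughly 6% to 18%.

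The upper end needs equal SDs and a low correlation, which restricted entry makes less likely. The lower end is effectively no excess. No figure in the article is wrong. This is an inexpensive improvement that serves the stated aim of not overpowering the main study, and it does not threaten the pilot's validity.

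**What to change.** In Objectives, in the pilot outcome under Primary outcome measures, and in Quantitative analyses, add to the variance of change the residual SD of 8–10-week PHQ-A from a model with arm and baseline PHQ-A. Report with it the baseline SD, the follow-up SD, the baseline–follow-up correlation and the SD of change, each with a 95% CI. State that the definitive trial will be sized on the variance that matches its planned analysis: the residual SD if it adjusts for baseline, the SD of change if it analyses raw change.

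The cost is one extra model on data already collected and a sentence in each of the three sections. No new assessment or participant is needed, and the existing pilot outcome is kept.

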#### Study population

Study participants will be adolescents aged 11 to 19 years with mild to moderate levels of depression.

#### Eligibility criteria

##### Inclusion criteria

Adolescents will be eligible for the study if as follows:They are aged 11 to 19 years on the date of consent (researcher confirms with parent/guardian at screening).Identified as having symptoms of mild to moderate depressive disorderAble to provide written consent or, if under age 16, written parental/guardian consent and written/verbal child assent (confirmed at baseline)Have access to a computer with Internet access or smartphone or device to use SPARX and must be able to install and log in (confirmed at baseline)They and their parent/guardian can read and write in English (confirmed at baseline).

##### Exclusion criteria

Adolescents will not be able to enter the study if ANY of the following apply:Clinical concerns that depression is too severe to benefit from SPARX and self-harm/suicidal risk is too highIntellectual disability or physical limitations precluding the use of SPARX (confirmed at baseline via CAIDS-Q)Had (in past 3 months) or currently having treatment with CBT/interpersonal therapy (confirmed at baseline)Has another major mental health disorder (e.g. psychosis, eating disorder) where the primary focus was not depression as confirmed by a clinician or DAWBASafeguarding concerns that are not currently being managed (i.e. the adolescent is the subject of a safeguarding investigation) as confirmed by a clinician

### Trial setting

This trial will be run online across England. Our main research sites are Oxford Health NHS Foundation Trust and Nottinghamshire Healthcare NHS Foundation Trust with multiple PICs covering several regions of England. Adolescents will be followed up at weeks 4 and 8–10 weeks after baseline.

### SPARX intervention

SPARX is a DHI for young people with mild to moderate depression and was designed as a stand-alone self-help intervention that can be accessed online via a computer or mobile phone/tablet app. SPARX was created to address the gap in adolescent depression treatment options, and it uses CBT techniques to address symptoms of depression. SPARX uses elements of fantasy gaming to engage the user in experiential learning with a Guide acting as a “virtual therapist” to explain how to use the skills learnt in the gaming environment into “real life”.

At the beginning and end of each module, the user interacts, in the first person, with a character called the “Guide”, who provides psychoeducation, gauges mood, and sets and monitors real-life challenges, equivalent to homework. The user is then transported to the “game world” to undertake interactive challenges. Upon successfully completing each module, the user returns to the Guide who puts the skills learnt in the game world into a ‘real-life’ context and sets a ‘challenge’ (i.e. CBT homework task) to facilitate skill generalisation. SPARX uses evidence-based CBT skills that focus on six ‘gems of power’ specifically: “Relax” (relaxation training), “do it” (e.g. behavioural activation), “sort it” (e.g. social skills training), “spot it” (recognising or naming cognitive distortions), “solve it” (problem-solving), and “swap it” (e.g. cognitive restructuring).

There are seven modules (or levels) in total, and each one lasts approximately 30 min. A breakdown of the core content of each module is outlined in Table 1.

**Table 1 Tab1:**
[figure not shown]
Core content in the seven modules within SPARX

After consulting with various stakeholders, the version of SPARX being used for this trial will retain the voice actors from the original New Zealand version. However, there will be differences from previous studies and the version available to the New Zealand public, including the following:No in-app measures or associated feedbackThe added ability to replay previously completed modulesLocalisation of specific guidance (e.g. signposting to UK-based not New Zealand-based support services)

### Human support

Participants randomised to receive supported SPARX will receive personalised guidance from an e-coach throughout their use of the intervention. The e-coach will provide limited contacts (less than 15 min per module) according to our study’s e-coach manual, as well as adherence reminders in case a module is not completed within 7 days. The feedback to be provided has the primary purpose of supporting, encouraging, and motivating participants, as well as promoting adherence to the intervention. In the supported arm, e-coaches will provide personalisation options to participants. This will include a choice of one or two modules being released per week and the contact modality (e.g. MS Teams/phone/email). E-coaches will also be able to access basic SPARX usage data for the participant(s) they are supporting throughout the trial. The e-coaches are psychology assistants, who are graduates in psychology and all work within CAMHS. They will be supervised by a Professor of Child and Family Mental Health with extensive clinical expertise working with adolescents (PS) and a researcher with a clinical background and extensive knowledge of SPARX (ML). The use of support whilst using SPARX has not been explored in any previous trials.

### Waitlist control group

The control group is a waitlist group. They will mostly be on waiting lists for services and will not have access to the SPARX intervention; however, they may receive support from other sources which we will capture at the primary endpoint via the concomitant interventions measure. Adolescents will receive £20 worth of Amazon vouchers for each assessment time point completed.

